##### Surveys

Participants in both arms are asked to complete web-based surveys using REDCap (Research Electronic Data Capture) [34]—a secure, web-based platform that participants used successfully in the preimplementation pilot study. The initial enrollment survey collects basic demographic and contact information including valid mailing address and phone number for the participant and an approved alternative contact, sexual orientation and gender identity items, and PrEP monitoring preferences. Subsequent interval surveys focus on evaluating self-reported PrEP adherence, number of sex partners, type and frequency of sex, frequency of drug or condom use, and measures of satisfaction with the assigned monitoring program.

##### Home Specimen Tracking

Participants in the HB-PrEP arm are contacted by study staff approximately 1 month before their visit (months 4, 8, and 16) to confirm whether they would prefer to come into the clinic or use a home sampling kit. Participants who opt for home sampling are sent a kit at that time to allow for samples to be received and results to be finalized before or near the date of their remote follow-up visit. Home sampling kits contain instruction sheets in English or Spanish, specimen labels, 2 swabs (Hologic Aptima 2 Combo, San Diego, California) for extragenital (or vaginal, if applicable) GC and CT testing, and 2 Tasso devices. The SHC’s protocol is not to offer men who have sex with men routine urine or urethral screening for GC and CT given that asymptomatic positivity at this anatomic site among men who have sex with men in our clinic is relatively rare and not felt to justify the cost of additional testing. Thus, consistent with our existing clinical protocols for in-person SOC, urine or urethral screening is not included in the home kits. Mailing and tracking of kits are managed through Tasso’s confidential kit delivery portal. Study staff enter participant information into the portal, at which point kits are assembled and mailed directly to the participant’s specified address. Tracking numbers allow staff to track the location of packages when they are received at the home, and when the participant arranges for pick-up to return specimens to the clinic. An automated text or email is then generated to notify participants that kits have been shipped and a reminder is sent 7 days after delivery if kits have not yet been returned.

##### Telehealth Visits and Interim Follow-Up

Participants in the HB-PrEP arm have 2 options for completing scheduled telehealth follow-ups: (1) through a telephone call with DRIS or (2) through a HIPAA (Health Insurance Portability and Accountability Act)-compliant Zoom conference call through the SHC electronic medical record. In addition, participants can reach study staff through WelTel—a secure and health information-compliant, 2-way message support program already in use by DRIS in our clinic for contacting PrEP patients [35]. Scheduled check-in visits for both arms consist of routine PrEP adherence counseling, screening for new HIV or STI symptoms, and PrEP prescription renewal if indicated. Per SHC protocols, participants with symptoms compatible with acute HIV or any STI must be evaluated in person in lieu of receiving a home sampling kit.

##### Specimen Processing and Laboratory Evaluations

Individuals randomized to HB-PrEP are mailed sampling kits to their preferred address and return self-collected samples through prepaid express postal mail to the PHSKC laboratory for processing within 48 hours. Participants are advised to refrigerate any sample that cannot be shipped and received in the clinic within 2 days (eg, over weekend days). Upon receipt in the clinic, the study staff and PI conduct a brief quality assessment of specimens, place laboratory orders in the electronic health record, and send samples to the PHSKC laboratory for testing per standard clinic protocol. Additional processing and testing procedures for HIV, syphilis, RPR, and creatinine have been described elsewhere [29].

#### Outcomes and Analyses

##### Primary Outcome Measures

Effectiveness will be evaluated with a survival analysis using PrEP nonretention as the event of interest. Observation time for all participants begins at the time of randomization and continues until either loss-to-follow-up or study end at 20 months. Consistent with previous studies [36,37], we define participants in either arm as “retained” on PrEP if they complete monitoring tests and visits with a clinician or DRIS at each 4-month interval to receive a renewed PrEP prescription. Kaplan-Meier curves will compare PrEP retention rates between the intervention and control arms at 20 months. We will use Cox proportional-hazards regression models to examine individual-level correlates (age, race and ethnicity, income range, and education status) of PrEP retention.

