Structural barriers such as lack of access to PrEP medical providers and the burden of quarterly clinical monitoring visits have stymied PrEP scale-up in the United States for years [7-9]. PrEP retention (defined as maintaining all aspects of PrEP care, including attending follow-up visits and obtaining monitoring tests every 3 months according to US guidelines [10]) represents a substantial gap in the PrEP care continuum [11,12]. Studies on national PrEP retention rates suggest only 56% of individuals who initiate PrEP remain on PrEP for at least 1 year, and only 41% persist through year 2 [13]. Younger age, Black race, and unstable or lower income are each associated with discontinuations and being lost to follow-up [14]. We have observed similar levels of PrEP retention in the PHSKC Sexual Health Clinic (SHC), with 40% of PrEP users discontinuing the intervention at least once within 12 months [15]. The COVID-19 pandemic created dramatic reductions in sexual health service capacity [16] that only further exacerbated and continues to impact existing structural barriers that lead to lower PrEP access and higher numbers of discontinuations [17-19]. Among sexual minority men newly diagnosed with HIV in King County, previous PrEP use and discontinuations are common and underscore the urgent need to develop and implement novel targeted strategies to minimize barriers and provide individuals with more options to stay on PrEP [20].

Home-based PrEP (HB-PrEP), whereby an individual self-collects PrEP monitoring specimens at home, mails them into a laboratory for testing, and follows up with a provider remotely to renew PrEP prescriptions, has the potential to decrease PrEP access barriers and increase PrEP continuation rates. Studies confirm that patients are comfortable self-collecting bacterial sexually transmitted infection (STI) screening specimens [21] and that HB-PrEP monitoring is acceptable and often preferable to in-person care [11,22,23]. Configuring PrEP programs to users’ needs can optimize both uptake and delivery [24]. Particularly for young sexual minority men, programs that are convenient, discreet, and provide them with agency over PrEP use and monitoring may reduce the stigma associated with PrEP use, and increase PrEP uptake and retention [11,23]. Furthermore, HB-PrEP may decongest high-volume clinical sites and create additional capacity to grow PrEP programs.

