**Inclusion criteria**
Age ≥18 years.Resident of Washington State.Can speak, understand, read and write in English or Spanish.Current pre-exposure prophylaxis user or interested in starting or restarting pre-exposure prophylaxis.Willingness to be randomized to home-based pre-exposure prophylaxis and adhere to specified procedures.Willingness to provide primary and alternate contact information.

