#### Randomization and Study Procedures

##### Sample Size and Power Considerations

Sample size calculations for the primary Kaplan-Meier survival analysis were based on standard methods [33]. Assuming that 2.5% of individuals discontinue PrEP per month in the control arm, we expect 45% of SOC participants to discontinue PrEP (55% retention) over the 20-month study period. In the intervention arm, we estimate that 70% will adopt HB-PrEP. We assume a relative risk of discontinuation of 0.6 among participants assigned to receive HB-PrEP leading to a 32% discontinuation rate (68% retention) in the HB-PrEP arm. We also allowed for an overall dropout rate in both groups of 6% [15]. Thus, a sample size of 458 participants should yield 80% power to detect a 13% point difference in PrEP retention. All eligible participants are assigned through simple 1:1 randomization to either the intervention arm (n=229) or SOC arm (n=229) and followed for 20 months. RCT procedures are detailed in Textbox 1.

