**Duration of current PrEP^b^ use, n (%)**		
	<3 months	3 (7)
	3-6 months	8 (20)
	6-12 months	6 (14)
	1-2 years	8 (20)
	>2 years	16 (39)

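### The stated correlates list omits baseline PrEP status and duration, and no stratification is named for the arm comparison, although starters, restarters and established users are pooled: a minor, cheaply mended weakness

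*Protocol article*

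**What the plan says.** All points are from the protocol article.

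- **Who enters.** The inclusion criteria admit "Current pre-exposure prophylaxis user or interested in starting or restarting pre-exposure prophylaxis". The recruitment section describes two pathways: existing clinic patients, and new or former patients.
- **How they are assigned.** Sample Size and Power Considerations: "All eligible participants are assigned through simple 1:1 randomization". No stratification factor is named.
- **How arms are compared.** Primary Outcome Measures plans Kaplan-Meier curves by arm at 20 months and names no stratification or adjustment.
- **Which correlates are modelled.** The same section: "We will use Cox proportional-hazards regression models to examine individual-level correlates (age, race and ethnicity, income range, and education status) of PrEP retention".
- **What is recorded at baseline.** Table 1 reports PrEP use status (42 currently taking, 5 planning to start) and duration of current use (under 3 months 3; 3-6 months 8; 6-12 months 6; 1-2 years 8; over 2 years 16).
- **What is known about retention over time.** The Background cites national data that "only 56% of individuals who initiate PrEP remain on PrEP for at least 1 year, and only 41% persist through year 2".

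**The concern.** The trial mixes people at very different points in their PrEP use. Among the 41 with a recorded duration, 16 (39%) had used PrEP for more than 2 years, while others had not yet started. If early use carries a higher risk of stopping, PrEP history is a baseline predictor of the primary event. It is collected, yet it has no stated place in randomization or analysis.

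Three things are at stake:

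1. **Correlates.** A model meant to explain retention leaves out time on PrEP. If age or income tracks time on PrEP (plausible, but not shown in the article), their coefficients will carry part of its effect.
2. **Chance imbalance.** Simple randomization does not balance the factor, and no adjustment is named to correct for it.
3. **Efficiency.** Stratifying on a prognostic factor usually adds some power, and the trial is planned at 80%.

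**Working it through.** **1. Reproducing the planned size.** The plan states: "Thus, a sample size of 458 participants should yield 80% power to detect a 13% point difference in PrEP retention". Taking its 45% and 32% discontinuation at 20 months as given, and assuming two-sided alpha of 0.05 (not stated):

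- Hazard ratio = ln(0.68)/ln(0.55) = 0.645.
- Schoenfeld's formula at 80% power needs 164 events.
- Average event proportion = (0.45 + 0.32)/2 = 0.385, so N = 164/0.385 = 426.
- Allowing 6% dropout: 426/0.94 = about 454, against 458 stated.

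The size reproduces within 1%. Conversely, 458 × 0.94 × 0.385 = 166 events gives 80.6% power.

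**2. Is time on PrEP prognostic?** From the 56% and 41% in the Background:

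- Year-1 hazard = -ln(0.56) = 0.580.
- Year-2 hazard = -ln(0.41/0.56) = 0.312.
- Ratio = 0.580/0.312 = 1.86.

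A starter does not keep the year-1 hazard for 20 months. Assuming the year-2 hazard stays flat afterwards:

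- Starter: 0.580 + 0.312 × 8/12 = 0.788.
- User at 1 year or more: 0.312 × 20/12 = 0.520.
- Ratio of cumulative hazards = 1.52.

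For everyone starting or under 1 year (5 starters; 3, 8 and 6 users at category midpoints of 1.5, 4.5 and 9 months), the cumulative hazards are 0.788, 0.754, 0.687 and 0.587. Their weighted mean is 0.692, and 0.692/0.520 = about 1.33.

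**3. The mix.** In Table 1, 5/47 (11%) were not yet on PrEP. Starters plus users under 1 year are (5 + 3 + 8 + 6)/46 = 22/46 (48%).

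**4. Chance imbalance.** SD of the between-arm difference in a factor's share = sqrt(4p(1-p)/458).

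| Share p | SD (points) | 95% range (points) | Shift in 20-month contrast per 1 SD, ratio 1.86 |
|---|---|---|---|
| 11% | 2.9 | ±5.6 | 0.6 points |
| 48% | 4.7 | ±9.1 | 0.9 points |

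Even at the edge of the 95% range, the shift with the 48% factor is about 1.96 × 0.94 = 1.8 points, against a planned difference of 13.

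**5. Power.** Simulated log-rank power, N = 430 (458 less 6%), visits every 4 months, 2,000 runs per row, whole-arm discontinuation held at the planned 45% and 32%:

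| Higher-risk share | Hazard ratio between strata | Unstratified | Stratified |
|---|---|---|---|
| 11% | 1.86 (from the article) | 79.6% | 80.3% |
| 48% | 1.86 (from the article) | 81.1% | 82.9% |
| 11% | 3.0 (assumed) | 81.4% | 83.5% |
| 48% | 3.0 (assumed) | 80.3% | 85.8% |

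Type I error was about 4-6% in every setting, stratified or not. The simulation standard error of each power is sqrt(0.8 × 0.2/2000) = 0.9 points.

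A further simulation let starters and recent users pass to the year-2 hazard, as in step 2 (8,000 runs, three strata). It gave 81.0% unstratified and 81.2% stratified. The gain on document-based figures is therefore about 0 to 2 points.

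**The case against.** The strongest reply is that the quoted Cox sentence concerns correlates of retention, not the arm comparison, and that the test and any adjustment set may lie in an analysis plan that is not shown. For the arm comparison this largely stands: the article does not commit to an unadjusted test, it only names no adjustment. The reply does not dispose of the point, because the article itself fixes the randomization method and the list of correlates, and that list omits a relevant variable the trial collects.

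Two stronger readings are tempting, and the documents do not support them.

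- **A reader might infer that the treatment effect will be attenuated.** The planned contrast is the difference in 20-month retention. Under randomization, omitting a baseline predictor does not attenuate a marginal difference of that kind. Attenuation concerns a conditional hazard ratio, which the article does not name as the primary estimand.
- **A reader might infer that the trial is underpowered.** The planning statement, "we expect 45% of SOC participants to discontinue PrEP (55% retention) over the 20-month study period", is a whole-arm rate. With whole-arm rates held fixed, unstratified power stays near 80% at both ratios in step 5. Power of roughly 70% to 76% appears only if 0.645 is taken as the within-stratum hazard ratio and the ratio between strata is assumed to be 3 or 5. Neither ratio has a source in the article.

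It is also fair to say that the prognostic evidence is indirect. It comes from national data on initiators, not from this clinic's patients or the trial's visit-and-test definition of retention, and no figure covers restarters. Chance imbalance is not bias.

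**Conclusion.** The point holds as a minor weakness. PrEP status and duration are recorded at baseline and are probably prognostic, yet they are missing from the stated correlates and from anything said about the arm comparison. The clearest cost is to the interpretation of the correlates model. For the arm comparison, stratifying would gain about 0 to 2 power points on the article's figures and would correct chance imbalance worth about 0.6 to 0.9 points per SD at a ratio of 1.86. Validity is not in question: type I error holds and 458 reproduces.

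This rests on the national hazards carrying over to this clinic, on a flat hazard after year 2 for the lower end of the range, and on a Table 1 mix taken from about 46 respondents among the first 100 enrollees. A lower hazard beyond year 2 would raise the gain, but the article gives no figure for it.

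**What to change.** Before arm-level retention data are analysed:

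1. Prespecify that the log-rank test and Cox comparison of arms are stratified by, or adjusted for, baseline PrEP status: existing patient versus starting or restarting. The enrolment pathway gives this for everyone.
2. Keep the unstratified Kaplan-Meier difference in 20-month retention alongside.
3. Add PrEP status and, where available, duration of current use to the Cox correlates.

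Duration should not define the stratum. It is self-reported by survey and Table 1 gives it for only 41 of the first 100 enrollees. As a correlate it needs a stated rule for missing values.

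The cost is wording; status needs no new data. One downside is that a stratified hazard ratio is a conditional estimand and should be labelled so, which is another reason to keep the marginal difference. The Discussion says retention analyses at 4 and 8 months are under way, so the change should be dated and should record whether results by arm had been seen.

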##### Secondary Outcome Measures

Reach is defined as the proportion of individuals assigned to the HB-PrEP study arm who choose to send in self-collected specimens from home for at least half of tri-annual PrEP visits over the study period. As we are interested in the real-world uptake of HB-PrEP, we are tracking and will report the total number of PrEP patients approached about the study, the number who declined participation and reasons for declination, and the proportion of individuals assigned to the intervention arm who choose at any time to transition to the SOC arm and reasons for doing so. To mitigate potential sampling (self-selection) bias, we explain in the screening process that even if randomized to the intervention arm, the use of HB-PrEP is optional, and patients in the intervention arm can always continue with standard in-clinic monitoring for some or all of the PrEP follow-up visits.

Acceptability or patient satisfaction with HB-PrEP will be evaluated using tri-annual web-based participant surveys including 5-point Likert scale questions adapted from questionnaires of similar PrEP trials. Additional items will inquire about the ease or difficulty of self-sampling device use, issues with receiving kits, and any other challenges with the home monitoring process. Specific validated psychometric tools to assess PrEP user satisfaction are limited overall and, to our knowledge, none exist that are designed to evaluate HB-PrEP services.

Study surveys inquire about PrEP use strategy (event-driven or “2-1-1” vs daily) over the preceding 4 months and adherence questions are tailored to the reported use strategy. Based on data that taking ≥4 doses/week confers a 96% reduction in HIV risk [38], self-reported PrEP adherence is measured using validated question items asking the percent of PrEP taken in the previous 4 weeks [39]. The percentage of PrEP adherence will be compared between arms and analyzed using linear mixed models to account for repeated measures on each participant.

We will measure the time from receipt of monitoring and STI results into the SHC electronic health record to the time study staff notify the participant of abnormal results.

We will also track new syphilis and GC or CT infections for each group per tri-annual interval to estimate a composite asymptomatic STI positivity incident rate.

##### Qualitative Data

Semistructured interviews will be conducted with HB-PrEP participants (n=24) beginning at month 4 and occur at triannual intervals thereafter, until recruitment goals are reached. The focus of these HB-PrEP participant interviews will be understanding specific barriers and facilitators of PrEP retention, identifying unanticipated negative effects or issues with the delivery of the intervention, determining whether HB-PrEP is preferred to SOC, and how future iterations of the program might be improved. Interview guides will be adjusted based on preliminary data from patient surveys to further explore any issues HB-PrEP participants identify. Clinic staff, including DRIS and administrators (n=3), will also be invited to participate in semistructured interviews at 12 and 20 months to understand operational barriers and facilitators of program implementation. Study participants and staff will be offered their choice of an in-person or virtual interview. Interviews will be audio recorded; transcripts will be independently reviewed by 2 study staff members and evaluated using thematic coding and a mix of inductive and deductive coding.

### Ethical Considerations

The study is considered human subjects research. All study procedures were reviewed and approved by the University of Washington institutional review board (IRB; STUDY00013871) and considered not to pose any more than minimal risk to study participants. Informed consent forms describing all study procedures, potential risks, compensation (if applicable), and contact information for the IRB and study staff were available in English and Spanish. Participation in the first study component (home-based monitoring vs SOC with web-based surveys) is not compensated. Patients and staff who participate in interviews for the qualitative study component will receive US $25 compensation.

All study staff are required to uphold strict confidentiality in accordance with the HIPAA. Only the information necessary to conduct the clinical trial or coordinate clinical care with providers will be viewed or used by authorized study staff. Home kits are in nonlabeled, plain boxes with no external information to identify study participants. Identifiable data is kept on an approved and password-locked database and only linked with indirect identifiers. Contributions in qualitative interviews will be deidentified and only general information used to derive themes for analysis.

## Results

### Overview

The HOT4PrEP trial is a hybrid implementation study that randomizes new or current HIV PrEP patients at the Sexual Health Clinic in Seattle, Washington, to have the option of home-based monitoring with self-collection of samples for HIV, syphilis, gonorrhea, chlamydia and creatinine and telehealth follow-up versus standard care including in-clinic visits and monitoring. The primary outcome is PrEP retention at 20 months.

Enrollment for the trial began in March 2022 and continued through May 2022 when all research was halted in the SHC to focus on the emerging mpox outbreak. Study enrollment then resumed in December 2022 and is ongoing.

From March 2022 to May 2023, a total of 161 PrEP patients were screened to enroll the first 100 participants into the intervention arm (49/100, 49%) or standard care arm (51/100, 51%). In total, 2 PrEP patients (1.2%) were deemed ineligible to enroll, 55 (34%) declined to participate, and staff were not able to discuss enrollment with 4 (2.5%) patients. Common reasons for declining to participate included preferring to come into the clinic or having an aversion to seeing blood during the self-collection process.

Table 1 describes demographics and other baseline characteristics participants self-reported upon enrollment. The baseline survey completion rate was 96% for both trial arms. Median age was 34 (IQR 28-39, range 19-67) years. Of the participants who elected to provide sex and gender information, all were assigned male sex at birth (47/47, 100%). Most identified as cisgender men (41/47, 87%), gay (42/47, 89%), and their race and ethnicity as non-Hispanic White (n=36, 38%) or Asian (n=23, 24%). Most participants reported an annual income of US $30,000 or more (75%) and at least some college education (91%).

All participants in the intervention arm were contacted before their 4-month follow-up visit to ask if they would prefer to come into clinic or receive home kits. Of the 49 participants contacted, 33 (67%) opted to collect samples at home and follow up through telehealth, 14 (29%) opted to come in person to the clinic, and 2 (4%) canceled their appointments. Of those who opted for home sample collection and telehealth follow up, 27 (82%) returned test kits with samples for HIV and STI testing, 5 (15%) came in person to the clinic for their visit, and 1 (3%) canceled their appointment.

**Table 1 table1:** Baseline characteristics of the first 100 home option testing for pre-exposure prophylaxis trial enrollees, March 2022-May 2023.

Characteristics		Values
Age (years), median (IQR)		34 (28-39)
Male sex assigned at birth, n (%)		47 (47)
